### **11.3.3 Secondary Analyses**

A mixed methods approach will be used for the pilot test to get quantitative (e.g. ratings on a 5-point Likert scale) as well as qualitative (e.g. awareness, perception) results.

In the intervention group, determinants associated with a change of medication will be identified and investigated by exploratory, multivariate regression analysis.

As a secondary analysis using the original data, a cost analysis will be carried out on the basis of present medication prizes, and costs saved by spared drugs and avoided hospitalizations will be estimated.

For process evaluation purposes we will explore barriers and enablers in terms of acceptance, feasibility and future use of our intervention, using semi-structured interviews or questionnaires within focus groups.

### **11.3.4 Interim Analysis**

Successful recruitment might be lower than expected. Therefore, we plan a first randomization step after the inclusion of 20 clusters (10 clusters per trial arm), i.e. 50% of the full sample size, with a subsequent interim analysis of this first set of clusters, while continuing with further recruitment. This should open the option for a partial publication/dissemination of results even for the case of a poor recruitment success. If the recruitment success will be closer to the sample size yielded, this two step randomization approach and the interim analysis will be dropped.

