## **2.8 Early Termination of the Study**

The Sponsor-Investigator and competent authority may discontinue the study prematurely according to the following circumstances:

- Ethical concerns
- Insufficient participant recruitment
- When the safety of the participants is doubtful or at risk, respectively
- Alterations in accepted clinical practice that make the continuation of a clinical trial unwise
- Early evidence of benefit or harm of the experimental intervention

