The envisioned number of 42 clusters (i.e. senior HPs; see sample size calculation in section 11.2) will be randomly allocated to two equally sized trial arms by an administrative member of the study staff using a software random number generator. After the training of the senior HPs, patient recruitment will be carried out by the senior HPs themselves or on their behalf by internship physicians or nurses; a person responsible for recruitment will be designated for every participating clinic/ward. All patients recruited by an individual senior HP or his delegates (on average 50 patients per senior HP) will be assigned to the respective senior HP's study arm, thus defining one cluster.

The participating physicians will neither be informed what study arm they belong to nor given specific details of the intervention of the other study arm. Similarly, the patients will not know whether their discharge follows the study (verum) or the "usual" (control) procedures.

The study and control interventions are explained in more detail in subsections 8.1.1 and 8.1.2, and data collection is laid out in sections 9.2 and 9.3. After follow up is completed for all included patients, the HPs in the control group will be debriefed and offered access to and training in the study instrument.

In a process evaluation study carried out in parallel to the RCT we will explore barriers and enablers in terms of acceptance, feasibility and future use of the study intervention, using semi-structured telephone calls or focus group interviews and questionnaires. As a secondary analysis using the original data, a cost analysis will be carried out on the basis of present medication prizes, and costs saved by spared drugs and avoided hospitalizations will be estimated.

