### **7.3 Assignment to Study Groups**

Clusters will be assigned randomly to the two equally sized study arms as soon as the required number of clusters is reached. Given the relatively small number of clusters (see sample size calculation in section 11.2) and since we expect considerable variation in hospital types and clinic sizes, careful consideration needs to be given to balancing the covariates listed in section 5.2. For the sake of simplicity in a setting where there is no need for overly sophisticated sequential allocation algorithms and in order not to sacrifice too much randomness for balance, we chose the following randomization approach:

- In a first step, simple randomization (the “sample” command of the statistical software package “R”) will be used to generate N complete and fully random allocation schemes, imposing no constraints regarding balance except for equally sized study arms.
- In the second step, a set of  $n$  ( $\ll N$ ) schemes with the lowest imbalances will be identified, using a similar criterion as in minimization techniques (for an overview see for e.g. (30)), or, alternatively, all schemes with a criterion value below some prespecified cut-off value.
- Finally, exactly one of these remaining schemes will be selected at random.

The whole allocation process will be carried out by an independent person not involved in planning the trial nor delivering the intervention nor collecting outcomes. The investigators will only receive the final allocation scheme from the person responsible for allocation. This list of senior HPs belonging to the intervention and control groups, respectively, will be kept at the study center.

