### 11.2 Determination of Sample Size

We modeled hospital readmission time by fitting an exponential survival curve on published readmission rates (48, 46) and internal data from the University Hospital Zurich. Extending readmission time by 25% was considered a relevant effect of the intervention. In the fitted model, this translates into an increase of the median readmission time by 23.2 days (from 92.7 days to 116.8 days) and corresponds to a hazard ratio of 0.80 between intervention and control group participants. This is equivalent to a decrease of 18.2% in readmission rates after 30 days (from 20.1% to 16.4%).

Based on this hazard ratio and assuming a two-sided  $\alpha = 5\%$ , a power of  $1 - \beta = 80\%$ , an intraclass correlation coefficient (ICC) of 0.02 as in (18), 40% overall censoring probability and equally sized clusters of 50 patients, we calculated a sample size of 21 clusters and 1'050 individuals per trial arm. Thus, 42 senior HPs and 2'100 patients in total will need to be included in order to observe a relevant effect of the study intervention with sufficient power.

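### The fallback interim analysis of 20 of 42 clusters may be published while recruitment continues, has no share of the 5% error rate, and does not match the one-step allocation in section 7.3

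*Protocol*

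**What the plan says.** Section 11.3.4 foresees that recruitment may fall short. It plans a first randomisation step once 20 clusters (10 per arm) are included, "with a subsequent interim analysis of this first set of clusters, while continuing with further recruitment". The purpose is stated: "This should open the option for a partial publication/dissemination of results even for the case of a poor recruitment success". If recruitment comes closer to target, both the two-step randomisation and the interim analysis are dropped. The synopsis likewise plans the interim only for poor recruitment.

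Section 11.2 sets a two-sided 5% level, 80% power, an ICC of 0.02, an effect that "corresponds to a hazard ratio of 0.80 between intervention and control group participants", and "40% overall censoring probability and equally sized clusters of 50 patients". From these, "we calculated a sample size of 21 clusters and 1'050 individuals per trial arm". It mentions no second look.

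Section 7.3 describes one allocation: "Clusters will be assigned randomly to the two equally sized study arms as soon as the required number of clusters is reached". It draws complete allocation schemes, keeps the best balanced and picks one at random. Section 6.1 also describes a single allocation, in which the 42 clusters "will be randomly allocated to two equally sized trial arms".

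Sections 6.1 and 6.3.2 rest the blinding on physicians and patients not knowing what the other arm does. Section 6.1 postpones the debriefing of control physicians until follow-up of all patients is complete.

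**The concern.** Three things do not fit together.

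- **Error rate.** The protocol foresees a look at randomised data that can be published and may be followed by a second analysis of a larger set containing the same clusters. The sample size assumes one test at 5%. If the first look is read at 5% and the final analysis is too, the trial has two chances of a false positive.
- **Release of results.** Section 11.3.4 does not require recruitment or follow-up to be closed before results are disseminated. Physicians and GPs in later clusters could learn what the intervention is and how it performed, which the blinding and the late debriefing are meant to prevent.
- **Allocation.** Section 7.3 selects among schemes for the complete set of clusters. It does not say how balance is kept if 20 clusters are allocated first and the rest later.

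At stake are the nominal level of the final test, the publication of a result from fewer than half the planned clusters, and the protection of clusters still enrolling.

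**Working it through.** **Inputs.** From section 11.2: hazard ratio 0.80, two-sided 5%, power 80%, ICC 0.02, 40% censoring (so 60% events), 50 patients per cluster, 21 clusters per arm. From section 11.3.4: interim at 20 clusters. From section 6.1: equal arms.

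**1. The plan's own sample size.** Schoenfeld events = 4(1.960 + 0.842)² / (ln 0.80)² = 630.5, rounded up to 631. Patients before clustering = 631/0.60 = 1,052. Design effect = 1 + (50 − 1) × 0.02 = 1.98. Patients needed = 1,051.7 × 1.98 = 2,082, or 1,041 per arm. That is 1,041/50 = 20.8 clusters, rounded up to 21 per arm: 42 clusters and 2,100 patients. The stated figure reproduces with the whole 5% spent on one test. Power at 2,100 patients is 80.4%.

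**2. Timing of the look.** With equal clusters, information fraction = 20/42 = 0.476. Section 11.3.4 calls this 50%.

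**3. Type I error with two unadjusted looks.** Under the null hypothesis the interim and final statistics are bivariate normal with correlation √(20/K), where K is the final number of clusters. The error is P(|Z₁| > 1.96 or |Z₂| > 1.96).

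| Final clusters K | 20/K | Correlation | Overall type I error |
|---|---|---|---|
| 20, one analysis | 1 | – | 5.0% |
| 24 | 0.833 | 0.913 | 6.9% |
| 30 | 0.667 | 0.816 | 7.7% |
| 36 | 0.556 | 0.745 | 8.1% |
| 42 | 0.476 | 0.690 | 8.4% |

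A simulation of cluster-level t-tests with 10 and then 21 clusters per arm (400,000 runs) gave 8.43% for K = 42, so the normal approximation is adequate.

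**4. Power at the look.** 20 clusters × 50 = 1,000 patients. Effective events = 1,000 × 0.60/1.98 = 303. Expected Z = √(303/4) × 0.2231 = 1.94, where 0.2231 = −ln 0.80. Power at 1.96 = Φ(1.94 − 1.96) = 49%. This assumes 40% censoring also holds in the first set.

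**5. Boundaries that keep 5% overall at 20/42.**

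| Rule | Interim p below | Final p below |
|---|---|---|
| Lan-DeMets spending, O'Brien-Fleming type | 0.0023 (z = 3.045) | 0.0492 (z = 1.967) |
| Haybittle-Peto at 0.001 | 0.001 (z = 3.291) | 0.0497 (z = 1.962) |

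Power of the final test at 0.0492 is Φ(2.815 − 1.967) = 80.2%, against 80.4% at 0.05.

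**The case against.** The strongest reply is that the interim is a contingency. Both the synopsis and section 11.3.4 tie it to poor recruitment, and it is dropped if recruitment comes close to target. The 42-cluster case, which gives 8.4%, is therefore the one in which the look is least likely to take place. This stands: 8.4% is an upper, conditional figure. It does not remove the point, because error exceeds 5% whenever recruitment goes past 20 clusters and both looks are read at 5%, and section 11.3.4 plans to go on recruiting. Nor does the protocol give a threshold or date for deciding that recruitment is poor.

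A second reply is that no interim test level is stated, and that boundaries are commonly left to a statistical analysis plan, which is not at hand. That is fair, and the absence of a boundary is not by itself the finding. The finding is the protocol's own combination of a publishable look during recruitment with a sample size built on one test, and an allocation section that does not allow for the look.

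Three stronger readings are tempting but not supported:

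- A reader might infer a formal efficacy test. Section 11.3.4 says only that there is an interim analysis; the publication option makes a between-arm comparison likely, but it is an inference.
- A reader might take section 2.8, which lists "Early evidence of benefit or harm of the experimental intervention" among termination grounds, as the stopping rule for this look. It is a general list, does not refer to section 11.3.4, and section 11.3.4 contains no decision to stop.
- A reader might conclude that later clusters will be contaminated. Publication is optional and its timing is not stated. With four months of recruitment and six months of follow-up, complete first-set data come about ten months after that set opens; whether other clusters would still be enrolling is unknown. It is a risk.

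Finally, section 7.3 can be read as the default and section 11.3.4 as a conditional variation. Even so, section 7.3 does not mention two steps, so the sections need aligning.

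**Conclusion.** The point holds in a conditional form. As written, the protocol permits a publishable interim analysis of 20 of 42 clusters during continuing recruitment, with no part of the 5% set aside for it. If both looks are tested at two-sided 5% and either counts as success, overall type I error lies between 6.9% and 8.4% for 24 to 42 final clusters. It is 5% if the trial ends at 20 clusters with one analysis. These figures assume equal cluster sizes and information proportional to the number of clusters. The look itself would have about 49% power for a hazard ratio of 0.80, so a null interim result would say little.

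It should be fixed before the first allocation. It is not a fatal flaw, because the look may never be taken and the repair is short.

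**What to change.** Choose one of two options in section 11.3.4:

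- **(a) No early comparison.** Make no between-arm comparison until follow-up of the last enrolled cluster is complete. A trial that ends short of 42 clusters then has one final analysis, at 5%, on the clusters it has.
- **(b) Keep the look with a boundary.** Pre-specify either the O'Brien-Fleming-type levels (about 0.0023 interim, 0.049 final) or Haybittle-Peto (0.001 and 0.0497). If recruitment ends at a number other than 42, recompute the final level from the actual information fraction. Release no results until all follow-up is closed.

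Under (b), also state the date and recruitment threshold that trigger the look, and give the fraction as 20/42 (47.6%). In either case align sections 7.3 and 11.3.4. If two allocation steps are kept, section 7.3 should say so and describe how balance is handled in each step, and the analysis should include allocation step as a stratum.

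The cost is one paragraph in section 11.3.4 and a sentence or two in section 7.3. The loss of power under (b) is below one percentage point. The real downside is that early partial publication is given up while recruitment or follow-up is running.

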### **11.3.5 Deviations from the Original Statistical Plan**

Necessary deviations from the original statistical plan will be duly substantiated and reported to the CEC at the earliest possible date.

## **11.4 Handling of Missing Data and Dropouts**

Dropouts will be recorded with reasons. A possible influence of the intervention on dropout probability will be analyzed by comparing dropout rates and dropout reasons between the two study arms. Missing data will be handled by multiple imputation, and in order to assess the imputation effect an additional complete case sensitivity analysis will be carried out.

## **12 ELIGIBILITY OF THE PROJECT SITES**

The Institute of Primary Care of the University Hospital Zurich will serve as the sole study center, while hospitals of all types, levels and legal structures are eligible as project sites. No study-specific infrastructure is needed at the project sites.

## **13 DATA QUALITY ASSURANCE AND CONTROL**

The Sponsor-Investigator warrants by implementing and maintaining quality assurance and quality control systems that the trial is conducted and all data is generated, documented (recorded), and reported in compliance with the protocol, GCP, and applicable regulatory requirements. Monitoring and Audits will be conducted during the course of the study for quality assurance purposes.

The study will strictly follow the protocol. If any changes become necessary, they will be laid down in an amendment to the protocol. All amendments of the protocol will be signed by the Sponsor-Investigator and, if essential, submitted to CEC.

### **13.1 DATA HANDLING AND RECORD KEEPING**

All electronic records and data will be kept under password protection at the Institute of Primary Care of the University Hospital Zurich.

#### **13.1.1 Case Report Forms**

The senior HPs will document the participation of each patient in an enrolment log (form 5a in the list of study instruments in appendix 18.1). One file of paper case report forms (CRFs) will be kept for each enrolled study participant, to be filled in completely and accurately with all relevant data pertaining to the participant during the study.

All requested information in the CRF should be completed in a neat legible manner. Use of a black ball pen will be recommended to ensure clarity of reproduced copies in the CRF. All corrections in a paper CRF shall be made in a way that does not obscure the original entry. The correct data must be inserted, dated and initialed by the investigator. Data that are not available or not done should be made clear by adding NA or ND. A declaration ensuring accuracy of data recorded in the case report forms must be signed by the investigator.

For data and query management, monitoring, reporting and coding the clinical data management tool "OpenClinica" will be used. The investigator will ensure that all data in the course of the study will be entered completely and correctly in the database. Corrections may only be performed by the investigator or by other authorized and identifiable persons. A list of all authorized persons with initials and signatures will be filed in the study site file and the trial master file, respectively. In case of corrections the original data entries will be archived in the system and can be made visible. For all data entries and corrections date, time and person who is performing the entries will be generated automatically.

Both the paper CRFs and the database will be kept current to reflect participant status at each phase during the course of study. Participants will be identified in the CRFs and the database by appropriate identification codes.

Essential documents including any patient files and source data will be retained for at least 10 years after the regular end or a premature termination of the study (ClinO Art. 45).

#### **13.1.2 Specification of Source Documents**

All original documents relating to the study (including but not limited to CRFs, logs, medical records from and correspondence with other departments or hospitals, if participant visited any during the study period or the post study period) as well as the medical history of the participants are considered source data. Source data must be available at the sites (study center, hospitals or GPs' offices) to document the existence of the study participants and substantiate the integrity of study data collected.

The following information (at least but not limited to) will be included in the source documents:

- Patient data (age, sex)
- Inclusion and exclusion criteria details
- Participation in study and signed and dated informed consent forms
- Medical history
- Key efficacy and safety data (as specified in the protocol)
- Related SAEs
- Results of relevant examinations
- Reason for premature discontinuation
- Randomization and identification numbers

### **13.1.3 Record Keeping/Archiving**

All study data will be archived at the study center (Institute of Primary Care, UniversityHospital Zurich) for a minimum of 10 years after study termination or premature termination of the clinical trial.

## **13.2 Data Management**

Relevant study data from paper log files and the patients' CRFs will be transferred to a digital database by a member of staff at the study center using the data capture software "OpenClinica". A second member of staff will supervise data entry into the database and both manual and software-assisted plausibility-checks will be applied to ensure data integrity.

The members of the study team will have exclusive access to the database stored on a central server of the UniversityHospital Zurich. "OpenClinica" will be used for data management, and periodic backups will be run according to the backup policy and schedules of the UniversityHospital Zurich.

## **13.3 Routine Monitoring**

Monitoring the project sites prior to the start and during the course of the study will help to follow up the progress of the clinical study, to assure utmost accuracy of the data and to detect possible errors at an early stage. Monitoring will be done primarily by phone and if needed by visits at the study/project sites.

All original data including the patient files (in particular all written informed consents and the CRFs), progress notes and copies of laboratory and medical test results must be available for monitoring. The accuracy of the data will be verified by reviewing the above referenced documents. The study center will collaborate with the Clinical Trials Center (CTC) of the University Hospital Zurich to ensure monitoring.

## **13.4 Audits and Inspections**

A quality assurance audit/inspection of this study may be conducted by the CEC. The quality assurance auditor/inspector will have access to all medical records, the investigators' study related files and correspondence, and the informed consent documentation that is relevant to this clinical study.

The investigators will allow the persons being responsible for auditing or the inspection to have access to the source data/documents and to answer any questions arising. All involved parties will keep the patient data strictly confidential.

### **13.5 Confidentiality, Data Protection**

Direct access to source documents will be permitted to the CEC for purposes of monitoring, audits and inspections, during and after conclusion of the study.

For contact maintenance and case tracking (e.g. in case of adverse events), the patients' identities will be known to a study nurse not involved in the analysis of the patient data. The patient names will not be accessible to the scientific study staff.

All electronic data, including interview transcripts, will be stored under password protection on secure network drives of the UniversityHospital Zurich.

## **14 PUBLICATION AND DISSEMINATION POLICY**

The study protocol will be submitted for publication in the BioMed Central journal “Implementation Science” (alternatively: “Trials”) before completion of patient recruitment.

After the statistical analysis of this trial the sponsor will make every endeavor to publish the data at medical conferences and in (a) medical journal(s). The results of the study will also be communicated to interested study participants, hereto using comprehensible language for patients and an appropriate scientific format for hospital and primary care physicians.

## 15 FUNDING AND SUPPORT

The following table gives estimates of the costs in CHF for individual stages/years of the study:

| Year                                                                                                                                                                                                                                                    | 2017                       | 2018                                            | 2019/2020                             |
|---------------------------------------------------------------------------------------------------------------------------------------------------------------------------------------------------------------------------------------------------------|----------------------------|-------------------------------------------------|---------------------------------------|
| Writing proposals, pilot test of material and procedures 
 
Scientific collaborator, 25%, 1 year
 
Study nurse, 50%, 6 months
 
                                                                     | 50'000
27'000
22'500 |                                                 |                                       |
| Cluster-randomized clinical trial 
 
Scientific collaborator, 50%, 2 years
 
Dissertant, 50%, 1.5 years
 
Study nurse, 50%, 2 years
 
Equipment, logistics, technical support, fees
 
 |                            | 135'000
55'000
25'000
45'000
10'000 | 112'500
55'000
12'500
45'000 |
| Implementation evaluation and cost analysis 
 
Scientific collaborator, 50%, 6 months, and 100%, 3 months
 
Dissertant, 50%, 1 year
 
Study nurse, 50%, 6 months
 
                           |                            |                                                 | 102'500
55'000
25'000
22'500 |
| Communication and dissemination                                                                                                                                                                                                                         |                            |                                                 | 10'000                                |
| Total per year                                                                                                                                                                                                                                          | 50'000              | 135'000                                  | 225'000                        |

The overall costs of the study are therefore estimated to amount to **410'000 Swiss francs**.

Funding of the project is provided within the National Research Programme "Smarter Health Care" (NRP 74) by the Swiss National Science Foundation with an amount of CHF 393'268.00 (request number 407440\_167193 / 1, granted on Dezember 7, 2016), payable in four yearly tranches:

|                            | 2017           | 2018           | 2019          | 2020          | Total          |
|----------------------------|----------------|----------------|---------------|---------------|----------------|
| Research funds             | 5'000          | 5'000          | 5'000         | 5'000         | 20'000         |
| Salaries                   | 103'562        | 111'907        | 64'867        | 44'242        | 324'578        |
| Social security taxes      | 15'535         | 16'787         | 9'731         | 6'637         | 48'690         |
| Total per year/grand total | 124'097 | 133'694 | 79'598 | 55'879 | 393'268 |

No other support is available from sources outside the Institute of Primary Care of the University Hospital Zurich.

